### Sample size calculation

The calculation of the required sample size for this RCT was conducted for the primary outcome, average pain intensity measured with a Numerical Rating Scale (NRS). Based on preliminary results of our single-arm explorative feasibility study and the RCT of Field *et al*, where a whole-food diet was implemented that restricts ultra-processed foods for pain management in chronic pain patients,^34^ we assume a pre-post correlation of r = 0.3. Although the single-arm trial found an effect (pre-post) of 1 SD, the expected effect size was set at 0.6 SD (–1.14).

For the CBT no pilot data were available. Therefore, the calculation of the effect size for this intervention was based on an RCT describing the efficacy of CBT in enhancing coping strategies, alleviating depression, stress, pain perception and improving the quality of life for women with endometriosis.^35^ In this study an effect of 0.55 SD was observed. For the current RCT this would translate to a similar effect of CBT as of the AIDI, so −1.14. We assume that the pre-post SD σ and correlation will be the same for all arms.

With 40 participants per arm, the precision for the main effects of AIDI and CBT yields an SD of 0.405, providing power greater than 80% for detecting an effect size of 1.14. However, the interaction effect has an SE of 0.57, ie, with a 95% CI for the estimated difference of ±1.12. This allows to observe an interaction effect in the order of magnitude of AIDI and CBT effects.

Based on our pilot-study we expect a dropout rate of 20–25%. Therefore, ten additional participants will be included in each arm of the RCT, resulting in a target sample size of 50 participants per arm, in total 200 women with endometriosis.

The evaluation of differences between HCs and women with endometriosis will be an explorative part of the study to generate preliminary insights. In the literature a sample size of 30–50 is described as a reasonable minimum sample size.^36^ Considering the potential drop-out and the group size in the other arms of the RCT, the total sample size for this RCT will be 250, of which 200 will be women diagnosed with endometriosis and 50 HC women.

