### Statistical analysis

Data collected via questionnaires will be analysed using the software IBM SPSS V.29 for Microsoft Windows, data regarding the biological samples will be analysed using R software. The threshold for statistical significance is defined as <0.05.

For the primary outcome, pain NRS scores, repeated measures ANOVA will be conducted with time (T0 vs T2) as the within-participants variable, group (SC, SC + AIDI, SC + CBT, and SC + AIDI + CBT) as between-participant variable, and the pain NRS score as the dependent variable. If there are missing data, or a temporary study halt, a linear mixed model will be used instead of repeated measures ANOVA. Model fit will be assessed with residuals vs predicted plots and observed vs predicted plots. An intention-to-treat analysis will be followed in the case of follow-up losses. In this analysis, participants are analysed according to their original group assignment, regardless of whether they completed the treatment or dropped out, to minimise the risk of bias due to selective dropout. Given the random assignment of the intervention groups, a regression analysis on the pre-post change, adjusting for the pre-intervention score will be used to measure the main effect of the AIDI and CBT, and estimate interaction effects. Mediation analysis will be conducted to understand if and how secondary outcome measures mediate the effect of the intervention on the primary outcome.

To investigate the differences between women with and without endometriosis at baseline, a Welch’s ANOVA will be performed. This method is chosen to account for unequal group sizes and variances. In case the data are not normally distributed, a non-parametric Kruskal-Wallis test will be used.

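### The Kruskal-Wallis fallback for the endometriosis versus healthy-control comparison drops the protection against unequal variances for which Welch's ANOVA was chosen

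*Protocol article*

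**What the plan says.** In the Protocol article, Methods and analysis, Statistical analysis, the test for this comparison is fixed in three consecutive sentences. First the test: "To investigate the differences between women with and without endometriosis at baseline, a Welch’s ANOVA will be performed". Then the reason: "This method is chosen to account for unequal group sizes and variances". Then the exception: "In case the data are not normally distributed, a non-parametric Kruskal-Wallis test will be used". The same section sets the level without exempting this comparison: "The threshold for statistical significance is defined as <0.05".

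The group sizes are in Sample size calculation, which gives the total "of which 200 will be women diagnosed with endometriosis and 50 HC women". That section also sets the status of the comparison: "The evaluation of differences between HCs and women with endometriosis will be an explorative part of the study to generate preliminary insights".

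**The concern.** Non-normality and unequal variance are separate features of the data, and finding the first does not remove the second. With two groups, Kruskal-Wallis is the Wilcoxon rank-sum test. Its reference distribution is derived under identical distributions in both groups, including identical spread. If centres agree but spreads differ, its actual level moves away from 5%, and the direction depends on whether the smaller group is the more or the less variable one. A 4:1 split makes this worse. The plan names unequal sizes and variances as its reason for Welch, then on one branch uses a test that handles the unequal sizes but not the unequal variances.

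At stake is the reliability of the list of markers reported as differing between patients and controls. Too many would be flagged if controls are more variable, and too few if they are less variable.

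**Working it through.** **Inputs.** Group sizes 200 and 50 (Sample size calculation). Level 0.05 (Statistical analysis). The ratio r of control SD to patient SD is not in the documents. It is an assumption here, shown over 0.5 to 2. The plan gives no figure of its own to reproduce on this point.

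**Large-sample formula, equal centres, normal data.** Let X be a patient with SD 1 and Y a control with SD r. F and G are their distribution functions.

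- Variance that Kruskal-Wallis assumes for the estimate of P(X<Y): (1/12)(1/200 + 1/50) = 0.08333 × 0.025 = 0.002083.
- Actual variance: Var[G(X)]/200 + Var[F(Y)]/50, with Var[G(X)] = arcsin(1/(1+r²))/(2π) and Var[F(Y)] = arcsin(r²/(1+r²))/(2π).
- Actual level: 2 × [1 − Φ(1.96/√k)], where k = actual variance / assumed variance.

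For r = 2: arcsin(0.2)/(2π) = 0.03205 and arcsin(0.8)/(2π) = 0.14758. The actual variance is 0.03205/200 + 0.14758/50 = 0.003112, so k = 1.494. The level is 2 × [1 − Φ(1.604)] = 10.9%.

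For r = 0.5 the two terms swap: 0.14758/200 + 0.03205/50 = 0.001379, so k = 0.662. The level is 2 × [1 − Φ(2.409)] = 1.6%.

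**Formula beside simulation (200 v 50, nominal 5%).**

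| SD ratio, control/patient | Kruskal-Wallis, formula | Kruskal-Wallis, simulated |
|---|---|---|
| 0.5 | 1.6% | about 1.8% |
| 0.67 | 2.6% | about 2.8% |
| 0.8 | 3.5% | about 3.5% |
| 1 | 5.0% | 4.7% |
| 1.25 | 6.8% | about 6.8% |
| 1.5 | 8.4% | about 8.6% |
| 2 | 10.9% | about 11% |

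In simulations at unequal SDs, Welch stayed at about 5% (4.9% to 5.2%) and so did Brunner-Munzel (4.8% to 5.7%).

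**Non-normal data, where the fallback would apply.** Ranks do not change under a monotone transformation, so the normal-data results carry over to lognormal markers with equal medians and unequal log-SDs. With log-SD 1 in patients and 0.5 in controls, Kruskal-Wallis rejects 1.6%; reversed, it rejects 11.1%. Welch on the log scale gives 5.1% both ways. For symmetric heavy-tailed data, Kruskal-Wallis at ratios 0.5 and 2 gives 1.8% and 10.5% (t with 5 df) and 2.1% and 9.7% (Laplace), while Welch stays at 4.7% to 5.1%.

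**Whole two-stage rule.** The trigger is assumed to be Shapiro-Wilk p<0.05 in either group. With t(5) data, about 87% of data sets switch to Kruskal-Wallis, and the overall level is 2.4% at ratio 0.5 and 10.0% at ratio 2.

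**Where the distortion is small.** With equal SDs and symmetric data at 200 v 50, Kruskal-Wallis gives 4.7% to 5.1%. With five groups of 50, symmetric data and one group's SD between a third and three times the others', it gives 5.2% to 6.1%.

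**Where Welch is imperfect.** On the raw scale it rejects about 6.6% for identical lognormal groups with log-SD 1. With equal-mean lognormals (log-SD 0.5 in patients, 1 in controls) it rejects 9.4%.

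**Power cost of Brunner-Munzel.** For a pure shift on the log scale, its power is 69.7% against 70.1% for Kruskal-Wallis.

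**The case against.** The strongest reply is that a rank fallback has a real purpose. With skewed markers, raw-scale Welch does not hold 5% exactly and can lose power. For a log shift of 0.4 at log-SD 1, Welch has 63% or 39% power depending on which group is higher, against 69% for Kruskal-Wallis. This stands. A reader might infer that Welch needs no normality at 200 v 50 and that the fallback should simply be deleted. The figures do not support that for strongly skewed data on the raw scale.

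Second, unequal raw variances do not by themselves invalidate Kruskal-Wallis. Two lognormal groups with the same log-SD and different means have unequal raw variances, and a rank test handles them well. The problem arises when spreads differ on a scale where centres agree, and the documents do not show this for any marker. That also stands: the plan's reference to variances may be a precaution, and the SD ratios above are assumptions.

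Third, ANOVA and Kruskal-Wallis are often used for more than two groups, and Study design describes five arms. If five arms of 50 were compared, little would be lost with symmetric data. However, the stated contrast is women with against women without endometriosis, and five planned arms of 50 would not be unequal in size. The plan's own reason therefore points to 200 v 50.

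Fourth, the comparison is explorative and non-randomised. This is correct and sets the severity. How normality will be judged is a detail that may sit in a fuller document, and it is not part of this point.

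**Conclusion.** The point holds in limited form. The fallback does not keep the property for which Welch was chosen. At 200 v 50, the actual level of a nominal 5% Kruskal-Wallis test runs from about 1.8% to about 11% over assumed SD ratios of 0.5 to 2. At the mild ratios of 0.8 and 1.25 it is about 3.5% and 6.8%. This rests on the two-group reading, on equal centres, and on spreads that really differ.

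A reader might infer that false positives will double. The documents do not support this, because they give neither a size nor a direction for the variance difference, and the error is conservative if controls are the less variable group. Nor does the point reach the randomised comparison of pain scores, which uses other methods. Low severity.

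**What to change.** Amend one sentence in Statistical analysis in either of two ways:

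- For the two-group comparison, name Brunner-Munzel in place of Kruskal-Wallis as the method for non-normal data. It tests whether values in one group tend to exceed those in the other, and it allows unequal spread. Report the estimated probability with its interval, since this is a different quantity from the difference in means under Welch.
- For skewed positive markers such as concentrations and hair cortisol, fix the log scale in advance and keep Welch on that scale.

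The cost is one sentence. It needs no additional data and has almost no effect on power. Standard functions exist in R, which the plan already uses for the biological samples; questionnaire scores, which are assigned to SPSS, could be run in R for this comparison. Recruitment is planned to the end of 2026 and the protocol has already been amended, so the change can still be made before the analysis.

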### Data monitoring

Monitoring will take place following the Dutch NFU Richtlijn Kwaliteitsborging mensgebonden onderzoek.^39^ Because of the negligible risk of the study, only minimal monitoring will be performed by the Radboud Technology Centre for Clinical Studies. An initiation visit will be done before inclusion of the first patient, one monitoring visit will be planned and a close out visit. The monitoring will include completeness of the Trial Master File, availability of signed informed consent forms, verification of the in- and exclusion criteria, check of accuracy on the described SAE’s and a check on the data management in Castor EDC.

### Premature determination of the study

The study can be terminated prematurely if there is evidence of an unacceptable risk for trial subjects, if there is reason to conclude that it is not feasible to collect the data necessary to reach the study objectives and it is therefore not ethical to continue and in case of failure of the investigator and/or staff to follow either good clinical practice standards or to adhere to protocol requirements. The decision to end the trial prematurely will be made by the coordinating investigators in close collaboration with the principal investigator.

### Ethics and dissemination

The study protocol has been approved by the METC Oost-Nederland from Radboud University Medical Centre on 11 July 2024, and was registered on ClinicalTrails.gov on 13 March 2024 (registration number: NCT06332560). After the first initial approval by the METC Oost-Nederland, amendments were submitted, all of which were approved. The latest version of the protocol is version 7 (1 October 2025). This study will be conducted according to the principles of the Declaration of Helsinki (V.2013) and in accordance with the Medical Research Involving Human Subjects Act (WMO).

The sponsor/investigator has a liability insurance which is in accordance with article 7 of the WMO. Due to the nature of the interventions the METC did not require the sponsor to take out additional insurance to cover non-negligent harm associated with the study protocol. Prior to participation, participants are required to provide informed consent. The first participant was included on 4 October 2024, and the aim is to attain all inclusions by the end of 2026. If participants wish to respectively start or continue the AIDI/CBT after the completion of the study, they are instructed to contact their gynaecologist or general practitioner for a referral to a dietitian or psychological therapist.

The results will be widely disseminated through scientific peer-reviewed journals, and presented to a broad audience in scientific meetings, congresses, patient meetings, as well as in policy relevant forums.

## Data Availability

Data sharing not applicable as no datasets generated and/or analysed for this study.
